## Abstract

**Background:**

Parent-mediated early interventions (EI) for children with autism spectrum disorder (ASD) can result in significant improvements in children’s cognitive ability, social functioning, behavior, and adaptive skills, as well as improvements in parental self-efficacy and treatment engagement. The common component to efficacious parent-mediated early interventions for ASD is clinician use of parent coaching and occurs when a clinician actively teaches the parent techniques to improve their child’s functioning. Available evidence suggests that community-based EI clinicians rarely coach parents when working with families of these children, although specific barriers to coaching are unknown. This consistent finding points to the need to develop strategies to improve the use of parent coaching in community EI programs. The purpose of this community-partnered study is to iteratively develop and pilot test a toolkit of implementation strategies designed to increase EI clinicians’ use of parent coaching.

**Methods:**

This study has four related phases. Phase 1: examine how EI clinicians trained in Project ImPACT, an evidence-based parent-mediated intervention, coach parents of children with ASD. Phase 2: identify barriers and facilitators to clinician implementation of parent coaching by administering validated questionnaires to, and conducting semi-structured interviews with, clinicians, parents, and agency leaders. Phase 3: partner with a community advisory board to iteratively develop a toolkit of implementation strategies that addresses identified barriers and capitalizes on facilitators to improve clinician implementation of evidence-based parent coaching. Phase 4: pilot test the feasibility and effectiveness of the implementation strategy toolkit in improving EI clinicians’ use of parent coaching with nine EI clinicians and parent-child dyads using a multiple-baseline-across-participants single-case design.

**Discussion:**

Completion of these activities will lead to an in-depth understanding of EI clinicians’ implementation of parent coaching in usual practice following training in an evidence-based parent-mediated intervention, barriers to their implementation of parent coaching, a toolkit of implementation strategies developed through an iterative community-partnered process, and preliminary evidence regarding the potential for this toolkit to improve EI clinicians’ implementation of parent coaching. These pilot data will offer important direction for a larger evaluation of strategies to improve the use of parent coaching for young children with ASD.

## Background

Parent-mediated early intervention for children with ASD results in improved child outcomes across a range of developmental domains, as well as improved parental self-efficacy and treatment engagement [1–5]. We use the term “parent” throughout to refer to any primary caregiver of a child, including biological parents, guardians, and other familial and non-familial caregivers. The common component to efficacious parent-mediated early interventions for ASD is clinicians coaching parents. Parent coaching includes providing the parent the needed supports to improve their child’s skills and abilities through a structured system of jointly planning learning goals, modeling effective practices, and engaging in feedback [6]. Clinician use of evidence-based parent coaching is hypothesized to result in parent behavior change, which in turn leads to improved child outcomes.

Parent coaching in early childhood is an interactive process between a clinician and a parent that involves observation, reflection, and action to directly promote the parent’s ability to support his or her child’s participation in family and community activities [6–8]. Most evidence-based coaching models are based largely on adult learning theory, which posits that adults benefit from specific strategies to motivate and teach them [9]. Examples of parent coaching strategies based on the adult learning theory are provided in Table 1. Increasingly, leaders in early childhood education recognize that clinicians should shift from the traditional role of providing therapy directly to the child to enhancing parents’ efforts at improving the child’s participation in daily routines [8]. EI programs that encompass the entire family, not only the child, align with the family-centered practices recommended by the Division for Early Childhood of the Council for Exceptional Children for use in early intervention [10]. Consequently, there have been increased efforts to train clinicians in how to coach parents [11, 12].

**Table 1 Tab1:** Examples of parent coaching strategies

Strategy	Description
Authentic learning experiences	Learning opportunities occur as part of real-life problems or challenges
Collaborative goal setting	Parent is actively involved in selecting goals and strategies for learning
Demonstration	Instructor models use of the technique through role-plays or actual application
In vivo feedback/guidance	Instructor observes parent’s use of strategies and provides immediate feedback
Reflection	Instructor engages parent in self-evaluation or assessment of performance

Despite these efforts, EI clinicians spend most of their time in traditional child-directed intervention, rather than in coaching parents [13, 14]. The reasons for poor implementation of parent coaching are unclear. Well-tested theories of behavior change can both provide insight into reasons EI clinicians do not use parent coaching and inform strategies to improve implementation. The theory of planned behavior posits that an individual’s intention to perform a certain behavior (in our case, use parent coaching) is the most proximal determinant of that behavior, when individuals have the ability to act on their intentions. Intentions are in turn influenced by three determinants: attitudes (e.g., whether one “likes” or “dislikes” using a given practice), norms (e.g., whether one perceives that using a given practice is expected by important others or whether one perceives that other similar practitioners use the practice), and self-efficacy (e.g., whether one believes that one has the necessary skills to perform the practice). This model is commonly used to predict health behaviors and has been used as a framework for understanding educators’ use of evidence-based practices (see Fig. 1) [15–17]. Previous work finds substantial variability in teachers’ and clinicians’ intentions to implement a new practice, and that intentions to implement a new practice are associated with its later implementation [16, 18]. Understanding EI clinicians’ intentions to implement parent coaching and whether these intentions are driven by attitudes, norms, and self-efficacy can lead to tailored implementation strategies that target specific mechanisms to increase use of parent coaching.

**Fig. 1 Fig1:**
[figure not shown]
Conceptual model of EI clinician implementation using the theory of planned behavior

Regardless of the theory underlying implementation strategies, those developed in partnership with community stakeholders are more likely to be used than those that were developed without stakeholder input [19–21]. Successful implementation of evidence-based practices is most likely to occur when the implementation process is developed in partnership with the individuals who will use them [21–23]. Including community stakeholder perspectives in developing implementation strategies improves their ecological validity and ensures that they are consistent with the community’s priorities, culture, and values [24, 25]. Using community-academic partnerships (CAP) offers a novel approach to developing strategies to support the implementation and sustainment of parent coaching [26].

A new initiative in Philadelphia’s EI system presents a rare opportunity to observe and improve EI clinicians’ implementation of parent coaching with families of young children with ASD. Through this initiative, clinicians working within the EI service system will be trained in Project ImPACT [27], an evidence-based parent-mediated treatment for young children with autism. Pilot data suggest that Project ImPACT can be successfully implemented in publicly funded EI service systems [4, 28] and shows promise for wide-scale implementation. However, in each of these evaluations, Project ImPACT was implemented by EI clinicians who were actively seeking training and were highly motivated to learn the skills needed to use parent-mediated interventions. It is not clear how EI clinicians working in a service system that is planning a wide-scale implementation will incorporate the program into their existing practice. Previous studies have found significant variation in educators’ motivation to adopt new evidence-based practices within large-scale rollouts such as this one [18]. Associated barriers to implementing evidence-based practices are exacerbated in large under-resourced service settings, like the early intervention system in Philadelphia [29, 30]. This training initiative is an important step in training EI clinicians to coach parents of children with, or at risk for, ASD. However, large-scale implementation and sustainment of new initiatives often require efforts beyond training and coaching, including the use of thoughtfully executed implementation strategies. Implementation strategies are defined as “methods or techniques used to enhance the adoption, implementation, and sustainability of a clinical program or practice” [31] and encompass a wide range of strategies targeted toward systems, organizations, and individual clinicians [32]. The proposed study takes advantage of this rollout to conduct a systematic evaluation of potential barriers and facilitators to implementation, with the goal of developing strategies to support the successful implementation of parent coaching among clinicians trained in Project ImPACT.

## Methods

### Setting

In Philadelphia, children 36 months of age and younger with or at high risk for ASD are eligible for publicly funded intervention through the infant and toddler early intervention program. Thirteen agencies provide these assessment and early intervention services in Philadelphia. They use an interdisciplinary treatment approach, have a treatment philosophy that supports parents to engage therapeutically with their children, and provide home-based services. In 2016, these agencies served 814 children with autism. EI administration selected three of these agencies to participate in the initial training for Project ImPACT. The current study will assess use of Project ImPACT in those initial training sites. These agencies are representative of the broader service system with regard to the number of clinicians employed (mean = 43 per agency) and the number of children with/at risk for ASD they serve (mean = 35 per agency in 2018). All agencies in Philadelphia EI serve the entire Philadelphia County; therefore, there is little variability across agencies in terms of the families they serve. All providers receive standard training delivered by the county. All agencies employ similar staff from a limited pool of educational backgrounds, including educators, speech pathologists, and occupational therapists.

### Project ImPACT

ImPACT stands for Improving Parents as Communication Teachers. Project ImPACT is a naturalistic behavioral developmental intervention (NBDI) that includes (1) a curriculum to guide parents in supporting their child’s social and communication skills using naturally occurring interactions and (2) guidelines to help EI clinicians coach parents in the use of the intervention strategies. Project ImPACT uses methods that emphasize fostering the child’s relationship with others to develop reciprocity, social engagement, and shared affect during adult-child interactions while incorporating behavioral strategies (e.g., direct prompting, contingency reinforcement) during a highly engaged interaction to teach specific social communication skills [27]. The program is delivered individually to parents of young children with or at risk for ASD in their homes during weekly EI sessions. EI clinicians help parents select appropriate goals for their child and train them to use intervention techniques to achieve those goals. For example, a clinician might explain to the parent that a strategy for increasing communicative requests would be to obstruct access to preferred items by placing them out of reach, then model the technique and coach the parent in how to use it during daily routines. Prior to implementing Project ImPACT, clinicians receive two days of didactic training regarding use of the program’s intervention and coaching techniques. Training includes role-play and practice, followed by monthly case consultation calls for 6 months.

### Phase 1: Examine EI clinicians’ current use of parent coaching when working with parents of young children with ASD

The primary research question driving phase 1 is how do EI clinicians trained in Project ImPACT implement the parent coaching aspects of the intervention? We hypothesize that (1) there will be substantial variability among clinicians in their use of parent coaching, and (2) clinicians will use certain coaching techniques (e.g., modeling of strategies) more often than others (e.g., in vivo feedback).

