#### Participants

We will recruit ten early intervention clinician/family dyads. EI clinicians will be recruited from the three publicly funded agencies participating in the Project ImPACT training initiative. Clinicians in these agencies are representative of clinicians in the broader service system with regard to professional background and children served on their caseloads. Recruitment will occur by randomly sampling without replacement from each agency, with the goal of recruiting evenly across the three agencies (i.e., 3–4 clinicians per agency). Inclusion criteria for EI clinicians will be as follows: (1) completed training in Project ImPACT prior to recruitment and (2) have at least three children with or at risk for ASD on his or her caseload. Families will be randomly selected from each EI clinician’s caseload. One family per clinician will be enrolled. Inclusion criteria for families will be as follows: (1) child that is less than 36 months of age; (2) child that has a classification of autism or high autism risk as determined by the EI system; (3) family that receives EI services through Philadelphia’s infant and toddler program; and (4) parent that speaks English or Spanish.

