#### Setting

Observations will occur in the family’s home, the usual setting for the provision of family-based early intervention services. One intervention session (approximately 1 h) with each of the ten EI clinicians will be video recorded by the research team.

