#### Measures

##### Clinician use of parent coaching

We will use the Project ImPACT Fidelity of Implementation for Coaching Form to measure EI clinicians’ fidelity to the parent coaching procedures outlined in the Project ImPACT manual [27]. This form is a 20-item observational tool that measures the clinician’s use of parent coaching techniques and has been used in a number of studies evaluating the effectiveness of Project ImPACT [4, 28, 33]. We will use the Triadic Intervention and Evaluation Rating Scale (TIERS) to measure EI clinicians’ use of collaborative coaching techniques. The TIERS is a validated observational tool designed to measure the use of parent-focused and collaborative coaching techniques within EI settings [34]. Both measures will be coded from video by the PI and trained coders.

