#### Data analysis

Descriptive statistics will be used to depict and compare clinician behavior. Clinicians’ coaching fidelity will be calculated using the metrics described in each measure including the mean, range, and distribution of overall fidelity scores and clinicians’ fidelity to the individual components of the coaching fidelity measures. This will increase our understanding of whether clinicians are more likely to implement certain aspects of parent coaching than others. To ensure validity of the fidelity ratings, 20% of sessions will be coded by a second observer. Consistent with recommendations for direct collection of data within clinical research [35], point-by-point inter-observer agreement data will be calculated as percent agreement by dividing the number of agreements between observers by the sum of both agreements and disagreements and then multiplying by 100 to yield a percentage [36]. We will also calculate Cohen’s kappa to ensure our reliability metric meets the highest standards of accuracy.

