#### Mixed methods data analysis

We will integrate the qualitative findings with quantitative measures of clinicians’ intentions, and determinants of intention, and findings from the observations during phase 1. We will use mixed methods in two ways. First, we will use quantitative findings to identify patterns in the qualitative data by entering quantitative findings (e.g., clinicians’ attitudes) into Nvivo as attributes of each participant. Then, as themes emerge from the interviews, we will use Nvivo to query whether the presence and quality of these themes differ among clinicians. Second, we will use the qualitative data to help interpret quantitative results, especially if there are counterintuitive findings. For example, if intentions are generally high but the fidelity is low, we will use qualitative interviews to specifically query participants about why they believe that to be the case. These data will help identify the areas of greatest need for the implementation strategy toolkit based on the theory of planned behavior.

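### Phase 1 hypothesis 2 leaves the coaching techniques to be compared open, and the planned descriptive comparison can hardly contradict it

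*Protocol article*

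**What the plan says.** The opening of Phase 1 in the Protocol article asks how trained clinicians implement parent coaching and states two hypotheses. The second is that "clinicians will use certain coaching techniques (e.g., modeling of strategies) more often than others (e.g., in vivo feedback"). No size of difference is given, and the two techniques appear only as examples.

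The data are small. Under Participants, "We will recruit ten early intervention clinician/family dyads"; under Setting, "One intervention session (approximately 1 h) with each of the ten EI clinicians will be video recorded by the research team". Under Measures, the coaching form is described: "This form is a 20-item observational tool that measures the clinician’s use of parent coaching techniques". A second scale is also coded: "We will use the Triadic Intervention and Evaluation Rating Scale (TIERS) to measure EI" clinicians' collaborative coaching; its number of items is not given.

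The Phase 1 Data analysis section plans descriptive statistics: mean, range and distribution of overall fidelity, and fidelity to the individual components. It then says what these are for: "This will increase our understanding of whether clinicians are more likely to implement certain aspects of parent coaching than others". In Phase 2, under Mixed methods data analysis, the Phase 1 observations are combined with interviews and survey measures, and "These data will help identify the areas of greatest need for the implementation strategy toolkit based on the theory of planned behavior". Table 2 has the findings of the observations, interviews and surveys presented at the second advisory board meeting.

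**The concern.** As worded, the hypothesis holds if some technique is used more than some other. With 20 items scored in ten sessions, the highest and lowest item means will almost surely differ even when true use is identical. A descriptive table of component means has no reference for how large a gap chance alone produces, so it can scarcely count against the hypothesis.

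What is at stake is modest but real. An item that looks least used after ten single sessions may be partly a chance extreme. It would be shown to the advisory board and would be one of several inputs when areas of need for the toolkit are identified.

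**Working it through.** The article gives no significance level, power, effect size or decision rule for Phase 1, so there is no figure of its own to reproduce. The check asks what the planned comparison shows when every item has the same true level of use.

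**Inputs from the article:** 10 clinicians, 1 session each, 20 items.

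**Assumptions (not in the article):** the form's scoring scale, the spread of ratings, and the correlation of items within a clinician. Ranges are shown for these. In the yes/no model, items are also taken as independent.

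**1. Yes/no items, common rate p.** Each item total is Bin(10, p). The chance that not all 20 totals agree is

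P(some differ) = 1 − Σₓ [C(10,x) pˣ (1−p)¹⁰⁻ˣ]²⁰, x = 0 to 10.

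The sum is 6.5 × 10⁻⁹ at p = 0.1 or 0.9, and smaller at p = 0.3, 0.5 and 0.7. A difference therefore appears with probability above 0.99999999. With only 5 grouped components (exponent 5 in place of 20), the probability is still 0.986 to 0.998.

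**2. Size of the chance gap, yes/no items** (200,000 simulated data sets per rate):

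| Common rate p | Median highest-minus-lowest gap | P(gap ≥ 30 points) | P(gap ≥ 50 points) |
|---|---|---|---|
| 0.1 or 0.9 | 30 points | 0.77 | 0.03 |
| 0.3 or 0.7 | 50 points | >0.99 | 0.76 |
| 0.5 | 60 points | >0.99 | 0.88 |

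**3. Rated items, assumed 1-5 scale** (20,000 data sets per setting; a clinician effect plus item noise, rounded and clipped to 1-5, equal item means; SD 0.8 to 1.2, within-clinician correlation 0 to 0.6). The mean gap runs from 0.7 (SD 0.8, correlation 0.6) to 1.3 (SD 1.2, correlation 0); at SD 1 and correlation 0.3 it is 1.0. A gap of at least 0.5 appears in 97 to 100% of data sets. Weaker item noise shrinks the gap: with a clinician SD of 1.0 and an item SD of 0.3 the median is 0.5.

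**4. The example pair alone.** For two equally used yes/no items,

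P(first strictly above second) = ½ [1 − Σₓ Bin(x; 10, p)²].

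At p = 0.1: ½ (1 − 0.3126) = 0.34. At p = 0.3: ½ (1 − 0.1932) = 0.40. At p = 0.5: ½ (1 − 0.1762) = 0.41. Rated items give 0.39 to 0.46. A named pair can therefore be contradicted by the data; the open wording hardly can.

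**5. What a named contrast could resolve with n = 10.** The half-width of a 95% interval for a paired mean difference is t₀.₉₇₅,₉ × SD/√10 = 2.262/3.162 × SD = 0.72 SD of the differences. A two-sided paired t-test at 5% has 80% power only for a standardised paired difference of about 1.0. An exact two-sided sign test needs 9 of 10 clinicians in the same direction (p = 0.021); 8 of 10 gives p = 0.109.

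**The case against.** The strongest reply is that the article never says any difference in item means will confirm hypothesis 2. It plans to depict and compare, and to increase understanding. A reader might infer that the hypothesis is confirmed essentially always, or that the plan cannot return a negative answer. The text does not support that: no confirmation rule is written, and on the hypothesis's own example the predicted direction arises by chance only 34 to 46% of the time. Had a gap of 50 points been required for yes/no items, chance support would range from 3% to 88% with the common rate. This stands, and it limits the point to a mismatch.

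A reader might also infer that the means of the 20 items are the only evidence. They are not: TIERS is coded, and range and distribution are reported. These add description, but neither gives a chance reference for a gap between items.

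Nor should one infer that the least-used items set the toolkit's content. Need is identified from integrated interview, survey and observation data; Table 3 sorts strategies by barrier, not by technique; and the second board meeting asks whether the findings reflect usual practice. That stands too.

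Finally, Phase 1 is exploratory, and a condensed article may leave tests and intervals to a fuller document. Their absence is therefore not the complaint. The complaint is that a hypothesis the article states is paired with an analysis the article also states, and the second cannot seriously test the first.

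**Conclusion.** The point holds as a mismatch between hypothesis and analysis. With equal true use of all 20 items, some difference is practically certain. Top-to-bottom gaps of roughly 30 to 60 percentage points (yes/no items, common rate 0.1 to 0.9) or about 0.7 to 1.3 points (assumed 1-5 scale) are what chance alone would produce. These sizes rest on the assumed scale, spread and correlation. They would shrink if items within a session were very strongly correlated, and for yes/no items they are smallest when use is very rare or near universal. The certainty that some difference appears hardly depends on these choices. It is a cheap improvement to data already planned, not an error that invalidates Phase 1.

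**What to change.** Either of two changes settles it.

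- **Make the hypothesis refutable.** Name modeling/demonstration versus in vivo feedback as the contrast for hypothesis 2, list the form items that make up each side, and report the within-clinician paired difference with a 95% interval. Describe rankings of the remaining items as exploratory, with intervals, when they go to the advisory board. An overall within-clinician test across items (for example Friedman, which gave 3.5 to 4.6% false positives in simulation under equal use) is optional.
- **Or reword hypothesis 2 as a descriptive aim,** so that no conclusion of support is implied.

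The cost is a sentence or two in the Phase 1 analysis and a few lines of code; no new data are needed. The first option requires that the form has separable modeling and feedback items, which the article does not show. With ten clinicians its interval will be wide, and hypothesis 2 may have to be reported as unresolved.
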